# Roux-en-Y gastrojejunostomy

Transecting jejunum was performed 25-30cm below treiz ligament after standard gastrectomy with lymphadenectomy. Side-to side jejuno-jejunostomy was performed 30-40cm below gastrojejunostomy.

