# Gastroduodenostomy

Gastroduodenostomy was performed using circular staple and the common channel was repaired by linear stapler after standard gastrectomy with lymphadenectomy.

Until now, no randomized controlled trial has been conducted for comparing the efficacy of DM improvement according to reconstruction type for gastric cancer surgery.

1. **Purpose**
2. Comparing the effect of improvement of hyperglycemia according to reconstruction type (Roux-en-Y gastrojejunostomy vs. gastroduodenostomy) in patients with gastric cancer and DM
3. Evaluating the mechanism of DM improvement according to reconstruction type.
4. **Place and period of the study**

Place: Severance hospital, Yonsei University College of Medicine

Periods: 2011.05.01~2014.04.30 (36 months)

1. **Selection criteria**

Inclusion criteria

1. Plan to underwent surgery for early gastric cancer, and in treatment for diagnosed DM and/or newly diagnosed DM in pre-operative check up
2. Location of tumor is lower part of stomach (possible cases of distal gastrectomy)
3. Age between 20-80
4. Understand the study and informed consent patients

Exclusion criteria

1. Patients who were treated by systemic inflammatory disease or with other malignancy
2. Uncontrolled co-morbidity
3. Vulnerable subjects (minor, pregnant women, lack of ability of recognition)
4. Severe complication after gastrectomy
5. **Sample size**

Retrospective study from our institution showed that proportion of patients who experience complete remission of DM, which was defined as no more necessity drug to control DM, was around 15% after gastroduodenostomy. It was reported that around 57% of patients who underwent Roux-en-Y gastrojejunostomy for gastric cancer with DM experienced remission of DM. Thus sample size for each group will be 18 for 0.05 of alpha and 0.20 of beta, and estimating 10% of drop-out rate, total 40 patients will be required.

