**<Methods>**

- Selecting patients who satisfy inclusion and exclusion criteria
- Randomization (without blinding):
  - Experiment arm: Roux-en-Y gastrojejunostomy
  - Control arm: Gastroduodenostomy
- Laboratory follow up: preoperation, post-operative day#7, #3months, #12 months
- Weight, fasting sugar level, post prandial 2hr sugar level, HbA1c, C-peptide (both of fasting and post prandial 2hr), lipid profile, insulin (both of fasting and post prandial 2hr), glucagon, IGF-1, GLP-1, Neuropeptide Y, Ghrelin, Leptin
- HOMA scale: HI=plasma glucose(mmol.L) x insulin(UI/ml)/22.5
- Comparing the outcomes between Roux-en-Y gastrojejunostomy and Gastroduodenostomy

1. **Variables**

-height, weight

-blood pressure, pulse rate

-duration of DM, duration of DM treatment, drug for DM

-insulin or not and amount

-pathology, postoperative morbidity and mortality

-Weight, fasting sugar level, post prandial 2hr sugar level, HbA1c, C-peptide (both of fasting and post prandial 2hr), lipid profile, insulin (both of fasting and post prandial 2hr), glucagon, IGF-1, GLP-1, Neuropeptide Y, Ghrelin, Leptin

- Laboratory follow up: preoperation, post-operative day#7, #3months, #12 months

-questionaire for quality of life

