**Statistical analysis**

- t-test, Chi-square test, Log-rank test, ANOVA test or Kruskal-wallis test

- HbA1c, C-peptide, lipid profile, Insulin, glucagon, IGF-1, GLP-1, Neuropeptide Y, Ghrelin, Leptin, HOMA scale: as an longitudinal data, comparing them by repeated measurement analysis of variance (RMANOVA) for comparing between Roux-en-Y gastrojejunostomy and Gastroduodenostomy

-two side p-value of less than 0.05 will be considered as statistical significance

1. Criteria for evaluation of safety, including side effects, evaluation methods and reporting methods

There are no changes in the existing surgical methods and data collection process, so there is no plan to report any postoperative complications or side effects.

1. Interim analysis

There is no planed interim analysis in this study.

1. Monitoring for data, process, and safety of this study

Investigator will do regular check.

1. Time table for the study

|  | **추진일정 (월)** | | | | | |
| --- | --- | --- | --- | --- | --- | --- |
|  | **0-1** | **2-13** | | **14-25** | **26-30** | **31-36** |
| **IRB Approval** |  |  | |  |  |  |
| **Patients’ enrollment** |  |  |  |  |  |  |
| **Data collection** |  |  |  |  |  |  |
| **Patients’ follow up** |  |  |  |  |  |  |
| **Analysis** |  |  |  |  |  |  |
| **Report** |  |  |  |  |  |  |

1. References

1) Joshua PT, David EC Cummings Hormonal and Metabolic Mechanisms of Diabetes Remission after Gastrointestinal Surgery. Endocrinology 2009 150:2518-2525

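### The protocol collects postoperative morbidity and mortality but says complications will not be reported; they should be described by randomised arm

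*Protocol*

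**What the plan says.** Four places in the Protocol bear on this.

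- **Variables** lists "postoperative morbidity and mortality" among the data to be recorded.
- **Criteria for evaluation of safety**, which follows the statistical analysis text, gives its reason first, "There are no changes in the existing surgical methods and data collection process", and then its conclusion, "so there is no plan to report any postoperative complications or side effects".
- **The two technique sections** describe different reconstructions. In the Roux-en-Y arm the jejunum is divided and a further anastomosis is made: "Side-to side jejuno-jejunostomy was performed 30-40cm below gastrojejunostomy". In the control arm, "Gastroduodenostomy was performed using circular staple and the common channel was repaired by linear stapler".
- **Exclusion criteria** ends with "Severe complication after gastrectomy", which can be judged only once the operation has been done.

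The Evaluation section names two things to be judged: improvement in diabetes laboratory values, and reduction of diabetes drugs or remission. It names no harm.

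**The concern.** The protocol lists harms data among its variables and then says it does not plan to report them. A statistical analysis plan may exist, but one written to this protocol would inherit the sentence, so this is more than a detail left for later.

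At stake is how the result can be read. The trial is an open-label randomised comparison in which the benefit is expected to be large: the sample size section assumes that "around 57% of patients who underwent Roux-en-Y gastrojejunostomy for gastric cancer with DM experienced remission of DM", against a control rate for remission "defined as no more necessity drug to control DM, was around 15% after gastroduodenostomy". If the safety sentence is followed to the letter, readers would see that benefit with no complications or deaths beside it in either arm.

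The exclusion adds to this. If it is applied after surgery, patients with a severe complication leave the data set. A morbidity table limited to those who remain would then omit the most important events.

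**Working it through.** This is mainly a comparison of texts. Arithmetic enters only to show what a descriptive table could deliver.

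**1. Collection against reporting.** Variables has morbidity and mortality recorded. The safety section has no plan to report any complication or side effect. Taken literally, the second statement leaves the first without a use.

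**2. Does the reason support the conclusion?** The reason is that surgery and data collection are as in existing practice. From this it follows that neither operation is experimental. It does not follow that the two have the same complications. The Roux-en-Y section adds a jejunal transection and a jejuno-jejunostomy that the gastroduodenostomy section does not contain. The background says that reconstruction type is unrelated to prognosis, which is not a statement about complications. Harms by arm are therefore a randomised comparison that the trial can make.

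**3. The exclusion.** The reconstruction is part of the operation, so a complication after it arises after allocation has taken effect. The drop-out section mentions only withdrawal of agreement and does not say how such patients are counted. If *k* of 20 patients in an arm are excluded for this reason, a table of retained patients shows 0/(20 − *k*) severe complications, where the full count is *k*/20.

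**4. Size of the arms.** The stated 18 per group and 10% drop-out give 36/(1 − 0.10) = 40, that is 20 per arm, as the protocol says. Exact enumeration of the two-sided likelihood ratio test at 18 per arm, 57% against 15%, also reproduces the stated power of 0.8091 and actual alpha of 0.0764. Nothing in this point alters those figures.

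**5. Precision of a table.** For zero events in *n* patients, the upper exact two-sided 95% limit is 1 − 0.025^(1/*n*).

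- *n* = 20: 1 − 0.025^(1/20) = 16.8%
- *n* = 18: 1 − 0.025^(1/18) = 18.5%

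For non-zero counts, the Clopper-Pearson limits are 0.1% to 24.9% for 1/20 and 1.2% to 31.7% for 2/20.

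**6. Illustration of step 3.** The counts here are assumed, not taken from the documents.

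| Excluded in an arm (*k*) | Retained patients only | All operated patients |
| --- | --- | --- |
| 0 | 0/20, upper limit 16.8% | 0/20, upper limit 16.8% |
| 1 | 0/19, upper limit 1 − 0.025^(1/19) = 17.6% | 1/20 = 5%, 0.1% to 24.9% |
| 2 | 0/18, upper limit 18.5% | 2/20 = 10%, 1.2% to 31.7% |

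The table shows the mechanism. It does not estimate how often it would occur.

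**The case against.** The strongest reply is that the sentence does not mean what it literally says. It sits under a heading that includes reporting methods, beside the items on interim analysis and monitoring. It may say only that, with established operations, no special safety-reporting procedure is set up. The text is partly untranslated, so one English verb should not carry much weight. Morbidity and mortality are listed, and the methods provide for comparing outcomes between arms, so nothing forbids a table. This largely stands: the documents do not show an intention to withhold harms. What remains is a sentence that says *any* complication, under a heading that also covers how safety is evaluated, and that can be followed literally.

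A second reply is that the exclusion concerns who is analysed and is a separate matter. That is fair for the efficacy analysis, which this point leaves alone. It does matter for the denominator of a harms table.

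A reader might also infer that, because far more patients are expected to stop diabetes drugs after Roux-en-Y, the protocol is wrong not to collect hypoglycaemic or hyperglycaemic episodes. The documents do not support this. Not naming such events is an omission, not a misstatement. Glucose, HbA1c, drugs, insulin amount and morbidity are already recorded. Nothing in the text gives a rate or direction of glycaemic harm by arm, and fewer drugs do not by themselves imply more hypoglycaemia. A recall question would be a new data item with gaps of up to nine months (3 to 12 months). In an open-label trial, with patients off drugs perhaps testing less, it could produce a spurious difference.

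**Conclusion.** The point holds as a minor one. The protocol lists morbidity and mortality as data and then disclaims reporting complications, for a reason that does not reach the comparison it randomises. Read literally, the result would be remission rates without harms by arm, and the post-surgery exclusion could hide the worst cases from a table of retained patients.

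This rests on two readings: that the safety sentence is taken as written, and that the exclusion is applied to patients already operated on. The documents settle neither, so the consequence is something that could happen, not something that will.

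A reader might infer that Roux-en-Y is the more harmful arm, or that the protocol's expectation of no specific additional risk is mistaken. Neither follows, because no complication rate is given for either reconstruction. No efficacy test, remission estimate or part of the sample size depends on this point.

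**What to change.** Replace the sentence in the safety section with, for example:

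> Morbidity and mortality after surgery, as collected under Variables, will be described by randomised arm: patients with at least one event, with exact 95% limits and no significance test. All randomised patients who had surgery are counted, including any later excluded because of a severe complication.

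The section on estimated side effects can stay as it is, and the variable list needs no addition. No hypoglycaemia or hyperglycaemia question is proposed.

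The cost is one sentence and one descriptive table, with no new visit, test or data item, provided that morbidity already recorded for operated patients is kept when a patient is excluded. The downside is low precision: with about 20 per arm, even an arm with no events is compatible with a true rate of up to 16.8%. The table should be presented as description and not as evidence that the arms are equally safe.
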